# Clinical Trial Protocol for “Replace Cysto”: Replacing Invasive Cystoscopy with Urine Testing for Non–muscle-invasive Bladder Cancer Surveillance—A Multicenter, Randomized, Phase 2 Healthcare Delivery Trial Comparing Quality of Life During Cancer Surveillance with Xpert Bladder Cancer Monitor or Bladder EpiCheck Urine Testing Versus Frequent Cystoscopy

**DOI:** 10.1016/j.euros.2024.02.018

**Published:** 2024-03-21

**Keywords:** Bladder cancer, Cancer surveillance, Urinary tumor markers, Bladder–cancer-specific quality of life

## Abstract

“Replace Cysto” is a multisite randomized phase 2 trial including 240 participants with low-grade intermediate-risk non–muscle-invasive bladder cancer, in which participants will be randomized 1:1:1 to one of two urine marker–based approaches alternating a urine marker test (Xpert Bladder Cancer Monitor or Bladder EpiCheck) with cystoscopy or to frequent scheduled cystoscopy. The primary objective is to determine whether urinary quality of life after surveillance is significantly improved in the urine marker arms. The primary outcome will be the patient-reported urinary quality of life domain score of the validated QLQ-NMIBC24 instrument, measured 1–3 d after surveillance. Exploratory outcomes include discomfort after surveillance, the number of invasive procedures that participants undergo per 1000 person years, complications from these procedures per 1000 person years, nonurinary quality of life, acceptability of surveillance, and bladder cancer recurrence and progression. Comparators include surveillance using (1) the Xpert Bladder Cancer Monitor test, (2) the Bladder EpiCheck urinary marker, or (3) frequent cystoscopy alone. After a negative cystoscopy ≤4 mo following bladder tumor resection, all the participants will undergo surveillance at 6, 12, 18, and 24 mo (with time zero defined as the date of the most recent bladder tumor resection). In the urine marker arms, surveillance at 6 and 18 mo will be performed with the marker. Regardless of the arm, participants will undergo cystoscopy at 12 and 24 mo. End of study for each participant will be their 24-mo cystoscopy. Overall trial duration is estimated at 5 yr from when the study opens to enrollment until completion of data analyses. The trial is registered at clinicaltrials.gov (NCT05796375).

## Introduction and hypotheses

1

### Current guideline recommendations

1.1

As per the current guideline recommendations, patients with non–muscle-invasive bladder cancer (NMIBC) undergo transurethral endoscopic resection followed by surveillance cystoscopy every 3–6 mo [1], making cystoscopy common with over a million procedures per year in the USA [2]. In spite of the burden that frequent cystoscopy procedures place on patients, high-quality data on the benefits of high-intensity surveillance cystoscopy conducted every 3–6 mo are lacking. The 3-mo time interval is due to historical precedent dating back to 1936 [3], and current guideline recommendations are based on expert consensus [1]. The experts writing the American Urological Association guideline recognized the unclear benefit of high-intensity surveillance and specifically stated: “There is an urgent need for studies to determine if less stringent follow-up regimens can be employed without significantly affecting oncological outcomes in these patients” [1].

### Urine testing as a less stringent follow-up regimen

1.2

One potential strategy to reduce the need for cystoscopy is to replace cystoscopy with less invasive urine-based tumor markers. Preliminary data show that the Xpert Bladder Cancer Monitor test (mRNA based) and Bladder EpiCheck (DNA methylation test) may replace cystoscopy procedures, given their overall sensitivities of, respectively, 0.72 and 0.74 in cross-sectional validation studies [4]. More importantly, their sensitivity to detect high-grade disease is 88% for Xpert Bladder Cancer Monitor and 91% for Bladder EpiCheck. Most urine markers have been used as an adjunct to cystoscopy to help detect “missed” cancer. White light cystoscopy can miss disease in up to 30% due to its overall sensitivity of approximately 70% when compared with enhanced cystoscopy [5]. However, there is potential for urine markers to replace cystoscopy since these have high sensitivity and a high negative predictive value (NPV) for high-grade disease (Table 1). However, patients with a positive or nondiagnostic urine test result will still need to undergo cystoscopy since the urine marker can portend the presence of cancer or the possibility of a false positive finding. With specificity of 0.76 and 0.84 (Table 1) [4], a patient without cancer will have a positive test for up to one in four times. To evaluate the role of urine markers in surveillance of patients, longitudinal comparative data are needed before these tests can be considered for routine care. Specifically, we need evidence that programmatic surveillance with urine markers decreases the burden of surveillance significantly for patients and has acceptable oncological outcomes in diverse populations of bladder cancer survivors.

**Table 1 t0005:** Available data on urine tests adapted from recent systematic review [4]

Test	*n* pat.	*n* stud.	Stage a	Grade a	Sensitivity all tumors	Sensitivity high grade	Specificity all tumors	NPV all tumors	NPV high grade
Xpert Monitor	2806	10	Ta: 1274 T1: 452	Low: 1214 High: 818	0.72 (0.63-0.80)	0.88 (0.79–0.96)	0.76 (0.72–0.81)	0.92 (0.90–0.94)	0.99 (0.98–1.00)
EpiCheck	1684	5	Ta: 725 T1: 482	Low: 672 High: 679	0.74 (0.57-0.86)	0.91 (0.85–0.97)	0.84 (0.80–0.88)	0.94 (0.90–0.97)	0.98 (0.96–1.00)

NPV = negative predictive value; pat. = patients; stud. = studies.

Sensitivity and specificity with 95% confidence intervals are shown based on pooled results from meta-analyses [4].

Note that the sensitivity for high grade and the NPV for high grade are based on a corrigendum to the original systematic review [27].

a Not all studies reported stage and grade; thus, the numbers presented here do not always add up to the total number of patients included in the studies [4].

### Sparing patients invasive cystoscopy procedures

1.3

Replacing cystoscopy with less invasive urine testing will spare bladder cancer patients many of the currently performed cystoscopy procedures. Cystoscopy can be quite uncomfortable for patients [6], as it is performed in nonsedated patients. According to a recent survey of bladder cancer patients, about half of patients experience moderate to severe discomfort during office cystoscopy, and almost 80% consider anxiety a problem associated with the procedure [7]. In a mixed-method study, two-thirds of the participants reported procedural discomfort or worry associated with surveillance cystoscopy [6]. In line with this, the majority of patients undergoing cystoscopy experience the procedure as bothersome and would choose a urine test if proven safe [8].

In preparation of the current protocol, the proposed trial was work-shopped with bladder cancer patients during a breakout session of the Bladder Cancer Advocacy Network’s “Summit” in October 2021. All 22 participants endorsed the study idea as highly or extremely important. This was driven by the negative connotations that cystoscopy brings to patients (word cloud in Supplementary Fig. 1) so that the majority (68%) felt that even avoiding one surveillance cystoscopy through the use of urine testing would be worthwhile.

### Observational studies suggest that less intensive cystoscopic surveillance is safe

1.4

In our observational study of 1042 patients with low-grade noninvasive Ta bladder cancer from the Department of Veterans Affairs, we found that frequent surveillance was not associated with any improvements in progression or bladder cancer death rates [9]. Similarly, among 1542 patients with high-grade noninvasive Ta bladder cancer from the Department of Veterans Affairs, there was no difference in bladder cancer death when comparing low- versus high-intensity surveillance [10]. This was in line with prior studies demonstrating no survival benefit of high-intensity surveillance using institutional [11] or SEER-Medicare data [12], [13]. These observational data suggest that less stringent follow-up with fewer cystoscopy procedures is probably safe from an oncological perspective. However, changing routine practice to less stringent follow-up by replacing invasive cystoscopy procedures with urine testing will require high-quality longitudinal data from prospective randomized trials such as the one described here.

### Urologists and patients are willing to replace cystoscopy with urine testing

1.5

One approach to low-intensity surveillance would be to simply decrease the intensity of surveillance cystoscopy, for example, by changing cystoscopy frequency from every 3–6 mo to once a year. However, such an approach could raise a concern among both patients and urologists that recurrent cancer could be missed, because the bladders of these patients would not be checked for an entire year. Replacing cystoscopy with urine testing provides an excellent middle ground between current practice with cystoscopy every 3–6 mo and cystoscopy once a year, as patients’ bladders will still be checked for recurrence while avoiding invasive cystoscopy procedures.

Urologists and patients are willing to replace cystoscopy with urine testing (see Supplementary Table 1) [14], [15]. In the preparation for this study, we discussed with urologists and patients regarding concerns about potentially missing cancer. This led us to choosing a study population of patients with low-grade intermediate-risk (according to the American Urological Association guideline [1]) NMIBC, which has very low rates of cancer progression to more dangerous invasive disease (see section 2.4. for details on these rates). Choosing this population allays concerns about missed cancer and danger associated with avoiding cystoscopy. Furthermore, the high sensitivity of the urinary markers for high-grade disease will result in the detection of nearly all progression or high-grade recurrence events.

## Design

2

### Overview

2.1

This is a phase 2 healthcare delivery parallel trial in which participants will be randomized 1:1:1 to programmatic surveillance with the Xpert Bladder Cancer Monitor or the EpiCheck urine test versus frequent cystoscopy at 6, 12, 18, and 24 mo (see the study schema in Fig. 1). Frequent cystoscopy is the standard of care according to current guideline recommendations [1], [16]. In the urine testing arms, urine testing will replace cystoscopy at the 6- and 18-mo marks.

**Fig. 1 f0005:**
[figure not shown]
Trial schema.

According to the PICOTS principle, this study addresses the following research question: in patients undergoing surveillance for low-grade intermediate-risk NMIBC (population), does programmatic surveillance in which cystoscopy is alternated with either the Xpert Bladder Cancer Monitor or Bladder EpiCheck tests (interventions) compared with frequent cystoscopic surveillance at 6, 12, 18, and 24 mo (comparator) decrease the burden of surveillance (significantly better urinary quality of life; outcomes) when started 3 mo after tumor resection (timing) in diverse outpatient urology practices (setting)?

Our study includes a pragmatic patient-centered design. This was driven by the desire to decrease suffering among bladder cancer survivors by replacing cystoscopy procedures with urine testing. Patients are very interested in this approach, given the burden associated with these procedures [6]. However, if urine tests do not improve quality of life, there is little rationale for further large studies.

We hypothesize that programmatic surveillance with urine testing will lead to significantly better urinary quality of life at the time points of interest at 6 and 18 mo than frequent cystoscopy.

### Interventions

2.2

Comparators include programmatic surveillance using (1) the Xpert Bladder Cancer Monitor test, (2) the Bladder EpiCheck urine test, or (3) frequent cystoscopy. After a negative cystoscopy ≤4 mo following bladder tumor resection, all the participants will undergo surveillance visits at 6, 12, 18, and 24 mo—a surveillance schedule that is in line with the current guideline recommendations [1], [16]. In the urine testing arms, surveillance visits at 6 and 18 mo will include a visit with the clinician and urine testing with the respective urine test; in case of a positive test result, the participant will undergo an immediate cystoscopy. In the frequent cystoscopy arm, surveillance visits at 6 and 18 mo will include a visit with the clinician and cystoscopy. Regardless of the arm, participants will undergo surveillance visits that include a visit with the clinician and cystoscopy at 12 and 24 mo (see the study schema in Fig. 1). Note that time zero is defined as the date of the most recent bladder tumor resection.

The 12- and 24-mo cystoscopy procedures were included in the urine testing arms for safety reasons. During the planning of this study, both urologists and patients were concerned about “missing cancer.” These cystoscopy procedures will assure that the maximal delay in finding a recurrent cancer in the urine testing arms will be no more than 6 mo. A 6-mo delay is highly unlikely to affect long-term outcomes in this intermediate-risk bladder cancer population, as these patients have only a 1% risk of cancer progression within 1 yr [17].

At the treating clinician’s discretion, any patient is allowed to undergo a for-cause cystoscopy, for example, for gross hematuria or new voiding symptoms. This provides additional reassurance that any participant’s bladder can be inspected directly as per the treating clinician’s discretion if believed to be necessary due to symptoms. Thus, the option to perform for-cause cystoscopy procedures will further minimize the risk of delay in diagnosis of cancer recurrence. Additional bladder cancer clinical evaluations and treatment will also be at the discretion of the treating clinician, and all evaluations and treatments will be recorded.

For the urine tests, participants will provide a voided urine sample during their surveillance visit. Samples will be collected and processed according to manufacturers’ instructions following a defined chain of custody and using standardized laboratory techniques. Currently, the Bladder EpiCheck test is cleared by the US Food and Drug Administration for use in conjunction with cystoscopy [18]. The current trial was approved as a nonsignificant risk device study by the governing institutional review board.

We will run monthly reports for each site to compare whether surveillance was administered according to randomized allocation. For any deviations of >10%, we will approach that site for retraining and technical assistance to optimize adherence to study interventions.

### Objective and outcomes

2.3

The primary objective is to determine whether urinary quality of life during surveillance is improved in the urine testing arms. We chose the primary outcome, patient-reported urinary quality life, based on (1) importance of the outcome to patients (Table 2) and (2) feasibility and rationale for evaluation in a phase 2 clinical trial. Oncological outcomes (eg, progression of disease) and complications were ranked highest by patients. However, progression and complications are rare and would require a very large study for adequate power. Discomfort was ranked third, and we considered this as the primary outcome. However, we felt that discomfort was too closely linked to the number of cystoscopy procedures that patients undergo in each arm. As such, this would clearly favor the urine testing arms, where patients undergo only two procedures instead of four scheduled procedures over the 2-yr study period (see the study schema in Fig. 1). For these reasons, oncological outcomes, complications, and discomfort were included as exploratory outcomes. Urinary quality of life 1–3 d after surveillance was ranked fourth and was chosen as the most meaningful and feasible primary outcome. For patients with a positive or nondiagnostic urine test, this outcome will be ascertained 1–3 d after the cystoscopy triggered by the urine test.

**Table 2 t0010:** Outcomes for the Replace Cysto trial

Rank	Outcome	How included in our study
1	Oncological outcomes, ie, not delaying detection of tumors	Exploratory outcome that will be assessed further in subsequent larger comparative effectiveness study if primary outcome is met
2	Complications of surveillance, eg, infections, strictures	Added as an exploratory outcome, not primary due to rarity of these events
3	Discomfort experienced after surveillance testing	Exploratory outcome, not primary as likely directly related to cystoscopy
4	Burden of surveillance, eg, urinary quality of life, anxiety	Primary outcome: urinary quality of life; exploratory outcome: anxiety
5	Number of cystoscopy procedures	Exploratory outcome

Rank indicates importance assigned by patients and caregivers, with “1” being most important. The five most important outcomes are shown out of a total list of nine reviewed with patients. These are previously unpublished data from workshopping the study with bladder cancer patients during the 2021 Bladder Cancer Advocacy Network’s Bladder Cancer Summit.

### Inclusion criteria

2.4

Based on discussions with patient advocates and bladder cancer experts, this study will include patients with low-grade intermediate-risk NMIBC, which present approximately a third of all patients. Patients will be enrolled if their surveillance cystoscopy ≤4 mo after bladder tumor resection is negative for recurrent bladder cancer. This population was chosen as it represents the optimal balance between the risk of cancer progression and opportunity to reduce intensity of surveillance.

Regarding cancer progression, urologists and patients may be worried about missing progression in the urine testing arms. In low-grade intermediate-risk patients, this is highly unlikely, as the risk of cancer progression within 6 mo is estimated to be <1% [17]. Furthermore, the time point with the highest risk for recurrence is the 3-mo time point after transurethral bladder tumor resection [19]. Thus, patients will be eligible for the trial only if they have a normal cystoscopy at the 3-mo time point, that is*,* ≤4 mo after the most recent tumor transurethral resection. This will further reduce inclusion of patients with a higher propensity for recurrence and progression of cancer. One additional safety feature is the high sensitivity and NPV of urine markers for patients with high-grade disease, so most progression events would result in a positive test.

Regarding the intensity of surveillance, guidelines recommend cystoscopy procedures every 3–6 mo [1]. Thus, urine testing has the potential to reduce substantially the number of procedures that these patients have to undergo. Currently, intermediate-risk patients undergo at least five surveillance visits in the first 2 yr after tumor resection, providing us adequate longitudinal data to compare the burden of surveillance across arms.

To be eligible to participate in this study, an individual must meet all the following criteria:1.Aged 18 yr or older.2.History of low-grade intermediate-risk NMIBC, defined as most recent pathology report showing any of the following:(a).*Multifocal low-grade* noninvasive urothelial carcinoma of any size(b).*Solitary low-grade* noninvasive urothelial carcinoma >3 cm in size(c).*Recurrent low-grade* noninvasive urothelial carcinoma

Note: A history of prior high-grade NMIBC is allowed, as long as the most recent pathology report showing bladder cancer does not show high-grade urothelial carcinoma, carcinoma in situ, or invasive carcinoma.

Note: Papillary urothelial neoplasm of low malignant potential should not be equated to low grade when assessing pathology for inclusion criteria.3.Stated willingness to comply with all study procedures and availability for the duration of the study4.No evidence for recurrence at cystoscopy ≤4 mo after the most recent tumor resection5.Ability to consent in English or Spanish

### Exclusion criteria

2.5

An individual who meets any of the following criteria will be excluded from participation in this study:1.History of total cystectomy of the bladder2.History of urinary diversion (eg, neobladder, colon pouch, or ileal conduit)3.History of muscle-invasive bladder tumor4.Known pregnancy or lactation (routine pregnancy testing is not required)5.History of urothelial carcinoma of the ureter or renal pelvis status after endoscopic treatment or with evidence of recurrent upper tract disease (inclusion allowed for status after nephroureterectomy and recurrence free at the time of inclusion)6.Anatomic constraints making cystoscopy impossible (eg, history of urethrectomy, obliterated urethra secondary to stricture)7.Inability to provide a voided urine sample

### Schedule of assessments

2.6

Participants in the urine testing arms who have a positive or nondiagnostic urine test will undergo cystoscopy no later than 1 mo after the urine test. For these participants, the outcomes listed below will be collected after undergoing a cystoscopy triggered by the positive or nondiagnostic test. Supplementary Table 2 summarizes the schedule of assessments.

#### Quality of life data (primary and exploratory outcomes) and complications (exploratory outcome)

2.6.1

The primary outcome is the patient-reported urinary quality of life domain score of the validated QLQ-NMIBC24 instrument, measured after surveillance. Exploratory outcomes include other QLQ-C30 and QLQ-NMIBC24 domains as well as anxiety and acceptability. These will be obtained by the clinical research coordinator via a phone survey 1–7 d after consent/randomization and after each surveillance visit via the general QLQ-C30 combined with the bladder cancer–specific QLQ-NMIBC24 [20], via the PROMIS Anxiety Scale [21], and via the Acceptability of Intervention Measure [22]. To encourage participation and to offset the burden of completing the quality of life surveys, participants will receive $20 per completed survey as a small token of appreciation for their time, effort, and inconvenience related to study participation.

For the purpose of collecting quality of life assessments, surveillance visits will be defined by the entire surveillance episode, which will include laboratory processing and communication of test results in the urine testing arms and, if applicable, also a cystoscopy triggered by a positive or nondiagnostic urine test.

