### Study setting and recruitment

2.7

Consecutive patients, 18 yr and older, undergoing surveillance for low-grade intermediate-risk bladder cancer will be approached for participation if their first surveillance cystoscopy ≤4 mo after tumor resection shows no evidence for recurrence. We anticipate that the population for this study will include individuals with diverse demographic characteristics from three locations throughout the USA (Charleston, SC; Dallas, TX; and White River Junction, VT). The protocol allows for opening the study at additional sides as needed.

Each site’s principal investigator will present the study protocol to the appropriate local clinical care providers so that those involved in the care of potential participants are familiar with the protocol requirements. Each site will have at least one dedicated clinical research coordinator to facilitate enrollment.

Each site’s principal investigator and clinical research coordinator will work with the clinical care team to identify patients scheduled for surveillance cystoscopy ≤4 mo after tumor resection, who meet the study inclusion criteria. The screening and recruitment procedures will include tracking of all screened and approached patients according to the Screening, Eligibility, Approach, Randomization (SEAR) framework [24].

Electronic health data will be used to identify potentially eligible patients. Specifically, study teams will regularly review lists of patients scheduled for cystoscopy procedures and lists of patients who underwent recent bladder biopsy or transurethral resection. These patients will then be prescreened for potential eligibility by clinical research coordinators using the electronic health record, with data recorded as part of the SEAR framework described above. After preliminary consultation and eligibility assessment by a potential participant’s clinical team, the participating site’s clinical research coordinator will approach each patient immediately after their surveillance cystoscopy to discuss enrollment and informed consent (see the Supplementary material for model informed consent form). We anticipate recruitment of 240 participants over approximately 3 yr.

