### Randomization

2.8

A participant will be enrolled in the study once screened for eligibility and after providing written informed consent. After enrollment, the clinical research coordinator will enter the patient study ID number and stratification factors (site, sex, and receipt of prior intravesical therapy) into the secure online Research Electronic Data Capture (REDCap) system [25] to obtain a study arm assignment. The assignment will be based on the randomization lists provided by the statistician. The list of randomization with 1:1:1 allocation is stratified by site, sex, and receipt of prior intravesical therapy, and was created with permuted blocks of size 6. Receipt of intravesical chemotherapy is defined as treatment with bacillus Calmette-Guérin (BCG) or with intravesical chemotherapy in the 12 mo prior to enrollment.

The clinical research coordinator will then convey the assignment to the treating clinician and participant, and assist with scheduling surveillance visits according to study arm assignment. Given the pragmatic nature of this healthcare delivery study, the participants, clinical staff, and clinical research coordinators cannot be blinded to intervention assignment. However, we will assure that interventions are coded in a way that analytical staff will be blinded to interventions until the analysis phase for the primary outcome is completed.

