#### Primary outcome analyses: urinary quality of life

3.2.2

The primary outcome is the patient-reported urinary quality of life domain score of the validated QLQ-NMIBC24 instrument [20], measured as a repeated measure at each surveillance visit. We will model the primary outcome urinary quality of life in terms of the study arm and time using a mixed-effect model with a random intercept for the participant. We will include fixed effects for the study arm (indicators for the Xpert Bladder Cancer Monitor and the EpiCheck urine test with the frequent cystoscopy arm as the referent, ie*,* intent–to-treat analyses), for time points (3, 6, 12, 18, and 24 mo) as categorical variables (3-mo baseline as referent), and the interactions of the study arm and time point. The interaction provides information about the treatment efficacy and is analogous to a difference in difference. We will also add a fixed effect for sex as a biological variable, given that women’s urethras are much shorter than men’s, which may very well affect urinary quality of life after surveillance testing. Results from these models will be presented as adjusted means with standard deviations.

As a complementary analysis, we will employ a generalized estimating equation (GEE) with the same fixed effects and cluster with respect to the participant using an autoregressive 1 correlation structure. As another evaluation of the robustness of findings, we will repeat the mixed effects and GEE analysis above, removing the 3-mo baseline value from the longitudinal vector of urinary quality of life and instead add it as a covariate (fixed effect) and eliminate the interaction from the model; the information on efficacy from these complementary analyses is in the main effects for the study arm. If these complementary analyses do not confirm the findings from the primary analyses, we will explore the reasons for the divergent results and report these with our main study findings.

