The hypothesis tests of primary interest are whether urinary quality of life scores are improved 1–3 d after surveillance with urine testing relative to surveillance with frequent cystoscopy. For participants with a positive or nondiagnostic urine test, this outcome will be ascertained 1–3 d after the cystoscopy triggered by the urine test. Each of the two urine test modalities will be compared with the frequent cystoscopy arm, using the Bonferroni-Holm method [30] to control the family-wise type 1 error rate at 5%. Each of these two tests (each urine test vs frequent cystoscopy arm) will be conducted using a multivariate Wald test that averages the corresponding coefficients from the 6- and 18-mo time points from the interaction of the study arm with time points. If there is a significant effect of urine test modalities (done at 6 and 18 mo) compared with the frequent cystoscopy arm, we will test whether the effect is different at 6 versus 18 mo.

All analyses will be performed using intent-to-treat principles and within the intent-to-treat population. For example, if a patient in a urine test arm does not complete a urine test and has a cystoscopy instead at 6 or 18 mo, we will nonetheless analyze this patient’s outcome data from this time point as in a urine test arm.

We do not anticipate that missing data will be a major issue as each site will have at least one staff member dedicated to obtaining the primary outcome data, that is, validated urinary quality of life domain scores, 1–3 d after the surveillance visit. Based on a similar prior longitudinal study validating the QLQ-NMIBC24 [20], we assume 20% missing data for the primary outcome at each time point.

Missing outcomes can be analyzed as is using the mixed-effect model for longitudinal data described above, under the assumption that the distribution of the outcome in participants for whom it is not missing does not differ from the distribution in those in whom it is missing conditional on previous observations of the outcome and covariates. We will also carry out sensitivity analyses to determine to what extent conclusions are sensitive to departures from this missing at random assumption. Our longitudinal analytic approach described above allows us to incorporate study data even if study visits were missed or participants were lost to follow-up.

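### The baseline quality of life survey is taken 1–7 days after open-label randomisation, so an arm-dependent reporting shift that fades by follow-up would bias the primary contrast

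*Protocol article*

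**What the plan says.** All references are to the protocol article.

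- **Timing (section 2.6.1).** The surveys are done "via a phone survey 1–7 d after consent/randomization and after each surveillance visit". Section 2.7 says that the coordinator "will approach each patient immediately after their surveillance cystoscopy to discuss enrollment and informed consent", so the first survey follows the negative cystoscopy that qualifies the patient.
- **Who asks (section 2.6.1).** "These will be obtained by the clinical research coordinator via a phone survey".
- **Who knows the arm (section 2.8).** Once REDCap returns the assignment, "The clinical research coordinator will then convey the assignment to the treating clinician and participant". The same section says that "the participants, clinical staff, and clinical research coordinators cannot be blinded to intervention assignment".
- **Use of the baseline (section 3.2.2).** The primary mixed model has fixed effects "for time points (3, 6, 12, 18, and 24 mo) as categorical variables (3-mo baseline as referent"). On the arm-by-time terms: "The interaction provides information about the treatment efficacy and is analogous to a difference in difference". The test of each urine arm "averages the corresponding coefficients from the 6- and 18-mo time points from the interaction of the study arm with time points". The complementary models with a baseline term move the same score to the covariate side.

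**The concern.** A baseline should be something that allocation cannot have touched. Here the first self-report is given by a participant who already knows the arm, to an interviewer in the role that conveyed it. Patients have a stake in the answer: section 1.3 says that most would prefer a urine test if it were shown to be safe. Some relief or disappointment in the first week is therefore plausible.

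The primary contrast subtracts this score. A temporary reaction at baseline would then appear, with its sign reversed, as a treatment effect at 6 and 18 months. The baseline-covariate models would condition on a variable measured after randomisation, so they give no clean check. Later analysis cannot recover an undisturbed baseline.

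**Working it through.** **Inputs from the article (section 3.1).** 80 per arm; exchangeable correlation 0.7; 20% missing at each time point; recurrence 10% and attrition 10% per year; sensitivity/specificity 72%/76% (Xpert) and 74%/84% (EpiCheck); effect 0.6 SD; two-sided 0.025 per comparison. Higher scores are better. Recurrence leads to withdrawal (section 2.6.4).

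**Assumptions.** Shift d of 0.1 to 0.3 SD in both urine arms, either sign; no benefit after a triggered cystoscopy; covariance treated as known. Results come from 1,000 to 1,500 simulated trials per scenario.

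**1. The plan's own figures.** Concordance: Φ(0.6/√2) = 66.4%, which matches the stated 66%. The stated 80% power was not reproduced: 98% if the SD is the total SD, 57–59% if it is the residual SD. These bracket 80% and the cells of Table 3 are not visible, so the stated power is not called wrong. The standard error below does depend on the scale.

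**2. How a shift enters.** Let Δ be the true contrast and k the fraction of the shift still present at 6 and 18 months.

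- Baseline after disclosure: expected contrast = Δ + kd − d = Δ − (1 − k)d. With k = 0 the bias is −d; with k = 1 it is 0.
- Baseline before disclosure: expected contrast = Δ + kd. With k = 0 this is Δ.

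**3. Yardsticks (total-SD scale).** With complete data, the standard error is √[2 × (1 − 0.7) × 1.5 / 80] = √0.01125 = 0.106 SD. With the stated missingness and withdrawal, the simulation gives 0.127 SD. Positive tests dilute the effect: in people without recurrence it is 0.6 × 0.76 = 0.456 (Xpert) and 0.6 × 0.84 = 0.504 (EpiCheck). Allowing for recurrences, the simulated contrasts are 0.446 and 0.491.

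**4. Result for a transient shift (k = 0).**

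| Size of d | Share of 0.446 / 0.491 | In standard errors | False superiority of at least one urine arm, Δ = 0, urine arms shifted down | Power at 0.6 SD, urine arms shifted up |
|---|---|---|---|---|
| 0 | – | 0 | 2.1% | 98% |
| 0.1 | 22% / 20% | 0.79 | 12–13% | 88% |
| 0.2 | 45% / 41% | 1.57 | 38% | 61–63% |
| 0.3 | 67% / 61% | 2.36 | 73% | 31% |

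Hand check for one arm at −0.1: 1 − Φ(2.24 − 0.79) = 1 − Φ(1.45) = 7.4%; the simulation gave 7.4% and 7.9%.

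On the residual-SD scale the standard error is 0.127/√0.3 = 0.23, so 0.1 SD is about 0.43 standard errors and the error rates would move less.

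**5. Other models.** With correlation 0.7, adjusting for baseline carries −0.7d, or 0.07 SD per 0.1 SD. A simulated common-baseline model gave 0.066 to 0.070. A comparison of the 6- and 18-month scores without baseline showed no bias from the baseline shift (estimates within 0.007 of 0 when Δ = 0). Its power at 0.6 SD is about 92%, against 98% for the planned contrast (total-SD scale).

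**The case against.** The best counter-argument is persistence. The follow-up scores come from the same unblinded people through the same coordinator role. If a reaction to the arm lasts, a baseline taken after disclosure subtracts it, while one taken before disclosure leaves kd in the estimate. This stands as arithmetic: for k above one half, the current order has the smaller distortion. But that cancellation relies on a persistence nobody has measured. A baseline untouched by allocation leaves the contrast with a plain meaning, the effect of assignment on the reported score, which is what the intent-to-treat analysis is meant to estimate.

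Other points also stand. Nothing in the article shows that this outcome shifts at all: it is a urinary domain, every arm has just had the same negative cystoscopy, and the first arm-specific visit is at month 6. The most natural mechanism, relief in the urine arms, works against superiority. The covariate models carry only part of a shift, and the article promises to explore and report divergent results. Supplementary Table 2, which holds the assessment schedule, is not shown, so identifying this survey as the 3-month baseline is an inference.

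A reader might infer that the primary result is bound to be biased, or biased in favour of urine testing. The documents support neither; the inflated false-superiority rates need urine arms to report worse at baseline, and no mechanism for that is given. Nor does the primary model rest on a common-baseline assumption that this timing would break, because it includes arm main effects.

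**Conclusion.** The point holds as an avoidable weakness in the order of data collection. The text supports each link: survey after randomisation, arm known to respondent and interviewer, and baseline differenced out of the primary contrast. The one-for-one bias of −d applies only to a shift present at baseline and gone by 6 and 18 months; in general it is −(1 − k)d. Size and direction are unknown. For assumed transient shifts of 0.1 to 0.3 SD the bias is 0.1 to 0.3 SD, roughly a fifth to two thirds of the diluted effect on the total-SD scale. The error rates in the table rest on that scale, which the article does not make visible. The change is worth making because it is cheap and cannot be replaced by later analysis.

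**What to change.** 1. After consent and the qualifying cystoscopy, complete the baseline survey before the REDCap assignment is drawn or disclosed. Ideally use the same 1–3 day window after cystoscopy as at follow-up; the present 1–7 day window is wider and runs from consent/randomisation.
2. Release the assignment when the survey is done or at the end of the 7-day window, whichever comes first, and treat an absent baseline as missing. A strict rule of no survey, no randomisation should be avoided: if the assumed 20% missingness applied at baseline, randomising 240 would need 240/0.8 = 300 consents.
3. For participants already enrolled, report baseline scores by arm and add a sensitivity analysis that compares the 6- and 18-month scores without the baseline score. This is immune to a baseline shift, though not to reporting differences at follow-up, and is somewhat less precise.

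The cost is a few days' delay in randomisation, and possibly some consented people who are not randomised. The sample size stays at 240.
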